### Follow up

Patients attending both 1 week and 5 week courses were invited to a 6 week post course group-based meeting lasting 1–2 hrs to review DAFNE principles (a standard practice for regular DAFNE course attendees). At 6 and 12 months post the last day of the course, both groups were due to attend for measurement of weight, recording of hypoglycaemic episodes, collection of blood for HbA_1c_ and blood biochemistry, and completion of psychosocial questionnaires. Interviews for the qualitative sub-study were conducted during the week after courses had concluded, with follow-up interviews six months later.

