**Methods/design:**

We aim to compare DAFNE delivered over five consecutive days (1 week course) with DAFNE delivered one day a week over five weeks (5 week course) in a randomised controlled trial. A total of 213 patients were randomised to attend either a 1 week or a 5 week course delivered in seven participating centres. Study outcomes (measured at baseline, 6 and 12 months post-course) include HbA_1c_, weight, self-reported rates of severe hypoglycaemia, psychosocial measures of quality of life, and cost-effectiveness. Generalisability was optimised by recruiting patients from DAFNE waiting lists at each centre, and by mailing eligible patients from hospital clinic lists. The inclusion and exclusion criteria were identical to those used to recruit to a standard DAFNE course (e.g., HbA_1c_ <12%, with no lower limit). Qualitative interviews were undertaken with a sub-sample of n=30 patients and their course educators (n=11) to help understand and interpret differences and similarities in outcomes between the 
two arms, and to identify logistical problems and unanticipated issues arising from the adaptation and delivery of 
a 5 week course.

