Some non-DAFNE centres have reported outcomes during routine care in self-selected individuals which are comparable to those reported in the original DAFNE trial [7]. Yet, since observational data of this type are prone to bias it is unclear whether such an extended approach to skills training is as effective as that provided on a 1 week intensive course. This randomised control trial is designed to test the hypothesis that the benefit of a structured education programme, with the identical contact time, is the same whether delivered over 1 or 5 weeks.

There are theoretical reasons why the two approaches might lead to different outcomes. A 1 week model might lead to stronger peer support developing over the week that could help to improve incorporation of self-management skills. Alternatively, a course delivered over 5 weeks might allow patients to gain more practice in self-management skills during the weeks between education sessions, thus facilitating integration of its principles into everyday life, and hence enhance sustainability. However, the potentially weaker peer support on a 5 week course may lead to a higher drop-out rate, with less participants completing the full 5 days of skills training.

Establishing whether DAFNE delivered at weekly intervals is as effective as delivering it over 5 consecutive days will help guide and inform decisions about future course delivery. Potentially it could also allow more individuals with Type 1 diabetes to receive structured education and increase patient choice. As qualitative work can provide important insights into trial outcomes [8], a qualitative sub-study was conducted in which we drew upon people’s understandings and experiences, by interviewing both educators and course participants. We also surveyed participants at the end of the trial asking whether they would prefer future structured education programmes to be delivered over 1 week or a more extended period of 5 weeks. Included in this survey were questions enquiring as to current self-management strategies.

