### Outcomes

We measured outcomes on two occasions primarily to examine the time of maximum effect, and also because repeated measures improves the power to test the main objective.

The Primary outcome was:

Change in HbA_1c_ from baseline at 6 and 12 months. HbA_1c_, a measurement of glycosylated haemoglobin, is regarded as the gold standard measure of glycaemic control reflecting overall blood glucose values over the previous 8–12 weeks. There is a strong relationship between HbA_1c_ and the risk of developing long-term diabetic complications and it is accepted as a reasonable surrogate for long-term outcomes in individuals with diabetes. HbA_1c_ was measured at local laboratories DCCT aligned (as per Diabetes Control and Complications Trial [10]).

The Secondary Outcomes were:

Change in HbA_1c_ from baseline at 6 and 12 months for those with a baseline HbA_1c_ ≥7.5%, This is because some of the participants with low HbA_1c_s would be aiming to reduce the number of episodes of hypoglycaemia, as opposed to further reducing their HbA_1c_.

Biomedical: eGFR, and lipids (including HDL cholesterol), using local labs at baseline and 12 months as part of routine clinical monitoring.

Hypoglycaemia: Number of episodes of severe hypoglycaemia using a standard definition of an episode leading to cognitive impairment sufficient to cause either coma or requiring the assistance of another person to recover. (The number of severe episodes is considered to be reliably recalled by patients for up to 1 year. [11])

Psychosocial:

• Quality of life: Quality of life (QoL) is assessed using both the diabetes-specific quality of life scale (DSQOLS [12]), and the generic measures of QoL, SF-12 [13], and EQ-5D [14].

• Emotional Well-being: is assessed using the Hospital Anxiety and Depression Scale (HADS; [15]), the diabetes-specific Problem Areas in Diabetes Scale (PAID [16]).

• Self-efficacy: Diabetes-specific self-efficacy is assessed using the Confidence in Diabetes Self-Care measure [17] a validated, reliable measure for people with type 1 diabetes.

• Thoughts about Diabetes [Personal Models of Diabetes [18,19]: This assesses beliefs about the seriousness of diabetes and treatment effectiveness. It is validated for use with adults with diabetes [20].

• Self-Care Behaviours: The revised Self-Care Inventory, a measure of perceived adherence to diabetes self-care recommendations [21].

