### Analysis

The primary analysis will be a linear model of HbA_1c_ at 12 months with baseline HbA_1c_ as a covariate, (which will improve the power relative to the predicted power), using generalised estimating equations (GEE) to control for clustering within courses. The intracluster correlation coefficient coefficient (ICC) will be estimated using the method of moments. Poisson regression (or a zero-inflated Poisson regression if necessary) will be used on the number of hypoglycaemic episodes over 12 months, which should also have more power than a dichotomy of having/not experiencing an episode, again using GEE to account for clustering. We will use an intention to treat analysis, but will explore the issue of participants dropping out using multiple imputations. The full analysis set (FAS) for the intention to treat analysis includes all patients for whom baseline data was collected. A per protocol analysis will also be performed.

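### The start of the 12-month severe hypoglycaemia count is not stated; the natural reading leaves about 28 course days unseen in the 5 week arm against 4 in the 1 week arm, and the count model may switch target

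*Protocol article*

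**What the plan says.** Under Follow up, the article schedules both visits from the end of training: "At 6 and 12 months post the last day of the course, both groups were due to attend". Among the tasks listed for those visits is "recording of hypoglycaemic episodes". The period that each visit asks about is not given.

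Under Analysis, Poisson regression, or a zero-inflated version if judged necessary, "will be used on the number of hypoglycaemic episodes over 12 months", "again using GEE to account for clustering". The section gives no start for the 12 months and no criterion for moving to the zero-inflated model. It names no covariate or time-at-risk term for the count, whereas the HbA1c model just before it names baseline HbA1c as a covariate.

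Under Outcomes, severe hypoglycaemia is a secondary outcome that relies on recall: "The number of severe episodes is considered to be reliably recalled by patients for up to 1 year". The Abstract speaks of rates of severe hypoglycaemia and lists it among outcomes collected before the course as well as after: "Study outcomes (measured at baseline, 6 and 12 months post-course". The Background gives a reason why the 5 week format might work differently: it might "allow patients to gain more practice in self-management skills during the weeks between education sessions".

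**The concern.** The last course day falls at a different stage of the intervention in each arm. In the 1 week arm it comes four days after the first session. In the 5 week arm it comes four weeks after, when patients have already been practising between sessions. For HbA1c, measured at a point in time, this anchor is harmless in form. For a cumulative count of events it decides which weeks are seen. A window that opens on the last day leaves out more on-intervention time in the 5 week arm, and that is the time in which the formats differ most.

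Two features of the model add to this. An open-ended switch to a zero-inflated model can change the quantity being estimated after the data are seen. And no baseline count is named, although the outcome is collected at baseline and the plan uses baseline adjustment for HbA1c to gain power.

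**Working it through.** **No figure to reproduce.** The article gives no rate, size or power figure for severe hypoglycaemia. Its sample-size calculation concerns HbA1c and does not enter here.

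**Inputs from the article.** Five consecutive days put the last session 4 days after the first. Five weekly sessions put it 4 × 7 = 28 days after. The count covers 12 months, taken as 365 days.

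**Assumed input.** k is the episode rate between the first and last session divided by the post-course rate. Post-course rates are taken as equal in the two arms.

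**Time unseen.** 28 − 4 = 24 more days in the 5 week arm, or 24/365 = 6.6% of a year.

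**Ratio over a common 365 days from the first session (5 week/1 week):** [(365 − 28) + 28k] / [(365 − 4) + 4k]

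- k = 0.5: 351/363 = 0.97
- k = 1: 365/365 = 1.00
- k = 1.5: 379/367 = 1.03
- k = 2: 393/369 = 1.07
- k = 3: 421/373 = 1.13
- k = 5: 477/381 = 1.25

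A window that opens on the last course day shows 1.00 in every row.

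**The same question under a different assumption.** Suppose instead that the rate is f times the later rate for the first 28 days after the first session in both arms, so that the formats are truly equal. The 1 week window, opening on day 4, still contains 24 of those days and the 5 week window contains none. The observed ratio is 365/(341 + 24f): 365/389 = 0.94 at f = 2, 365/413 = 0.88 at f = 3, 1.00 at f = 1 and 365/353 = 1.03 at f = 0.5. Size and direction agree with the list above.

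**Patients without a last course day.** Patients were randomised after baseline data collection, and the full analysis set is everyone with baseline data. Over 11% were lost between randomisation and course participation. If that share held for all 213 randomised, 0.11 × 213 ≈ 23 patients have no date from which a last-day window could open.

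**Why moving the start requires an offset.** Counting from the first session to the 12-month visit gives 365 + 28 = 393 days against 365 + 4 = 369. With k = 1 and no offset the ratio would be 393/369 = 1.07 from exposure alone. With log time at risk as offset it is 1.00 at k = 1, (421/393)/(373/369) = 1.06 at k = 2 and (449/393)/(377/369) = 1.12 at k = 3.

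**Incomplete follow-up.** If some patients are seen for only 6 months and no offset is used, the ratio is (1 − 0.5d₅)/(1 − 0.5d₁), where d is the share affected in each arm (assumed). It is 1.00 at 10% in both arms, 0.925/0.975 = 0.95 at 5% (1 week) against 15% (5 week), and 0.875/0.975 = 0.90 at 5% against 25%.

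**Zero-inflated model.** With a share π of structural zeros and count mean μ, the overall mean is (1 − π)μ. The count part estimates μ₅/μ₁. The overall ratio is (1 − π₅)μ₅ / [(1 − π₁)μ₁]. The two agree only if π is the same in both arms.

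**The case against.** Three stronger readings are tempting, and the article supports none of them.

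*The plan excludes the course weeks.* A reader might infer this, but Follow up fixes when visits take place, not the period they ask about. The 6-month visit could ask about episodes since baseline, and the course weeks would be well within the one-year recall limit. A window from the last day could also be chosen deliberately, to give both arms an equal period after training. What stands is that the start is not stated, that the three sections together point most naturally to the last course day, and that this choice would drop unequal time on the intervention.

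*The window makes the 5 week format look safer.* That holds only if the rate during the course exceeds the later rate. No rate is given, equal rates produce no distortion and lower ones reverse it. The Background reports that the original trial saw no increase in severe hypoglycaemia, which lends no support to a doubled or tripled rate, though it does not describe the weeks between sessions either. Nor does the article call this the main safety outcome; it is one of many secondary outcomes.

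*The model ignores follow-up time and baseline, so short follow-up is counted as a full year.* The article gives the count model one sentence, and the analysis plan is not shown. Silence there is not a stated omission. The Abstract's reference to rates is compatible with time at risk, and drop-out is to be explored by multiple imputation. Leaving out a baseline covariate costs precision but does not bias a randomised comparison.

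The zero-inflated option is different in kind: the switch is written into the plan without a criterion.

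**Conclusion.** The concern holds in a limited form. The start of the 12-month count needs to be stated. If it is the last course day, 24 more days of on-intervention time are unseen in the 5 week arm than in the 1 week arm, and the window is undefined for randomised patients who never began a course. The effect on the rate ratio is about 7% or 13% if the course-period rate is 2 or 3 times the later rate, nil at equal rates, and about 3% the other way at half the rate. These figures rest on an assumed k and on equal post-course rates; the article supplies neither.

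The unspecified switch to a zero-inflated model is a stated weakness, because its count part does not estimate the overall rate ratio. Adding the baseline count would be a nearly free improvement in precision, by an amount that cannot be computed from the article, and it corrects no bias. The time-at-risk term matters only where follow-up time is unequal.

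**What to change.** - **Window.** State when the count starts. Count severe episodes from randomisation, or from the first scheduled day of the allocated course, to the 12-month visit. Either start also covers randomised patients who never attended; for them the allocated course's scheduled dates can set both ends. If the window cannot be moved, report course-period episodes by arm where they can be recovered.
- **Model.** Pre-set one analysis, such as the Poisson GEE already planned, with robust variance and course clustering. Add log time at risk as offset, which a moved start makes necessary, and the baseline count as covariate. Keep zero-inflated Poisson as a sensitivity analysis only.

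The cost is slightly more analysis work, and recall a little over a year if course-period episodes were not asked about by 6 months. Data collection was due to end by Summer 2012 and the article appeared in November 2012, so a new question to patients may come too late. The programme database described under Health economics analysis records contacts for hypoglycaemic events and could recover some course-period episodes, but only those that led to a recorded contact.

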### Outcomes

We measured outcomes on two occasions primarily to examine the time of maximum effect, and also because repeated measures improves the power to test the main objective.

The Primary outcome was:

Change in HbA_1c_ from baseline at 6 and 12 months. HbA_1c_, a measurement of glycosylated haemoglobin, is regarded as the gold standard measure of glycaemic control reflecting overall blood glucose values over the previous 8–12 weeks. There is a strong relationship between HbA_1c_ and the risk of developing long-term diabetic complications and it is accepted as a reasonable surrogate for long-term outcomes in individuals with diabetes. HbA_1c_ was measured at local laboratories DCCT aligned (as per Diabetes Control and Complications Trial [10]).

The Secondary Outcomes were:

Change in HbA_1c_ from baseline at 6 and 12 months for those with a baseline HbA_1c_ ≥7.5%, This is because some of the participants with low HbA_1c_s would be aiming to reduce the number of episodes of hypoglycaemia, as opposed to further reducing their HbA_1c_.

Biomedical: eGFR, and lipids (including HDL cholesterol), using local labs at baseline and 12 months as part of routine clinical monitoring.

Hypoglycaemia: Number of episodes of severe hypoglycaemia using a standard definition of an episode leading to cognitive impairment sufficient to cause either coma or requiring the assistance of another person to recover. (The number of severe episodes is considered to be reliably recalled by patients for up to 1 year. [11])

Psychosocial:

• Quality of life: Quality of life (QoL) is assessed using both the diabetes-specific quality of life scale (DSQOLS [12]), and the generic measures of QoL, SF-12 [13], and EQ-5D [14].

• Emotional Well-being: is assessed using the Hospital Anxiety and Depression Scale (HADS; [15]), the diabetes-specific Problem Areas in Diabetes Scale (PAID [16]).

• Self-efficacy: Diabetes-specific self-efficacy is assessed using the Confidence in Diabetes Self-Care measure [17] a validated, reliable measure for people with type 1 diabetes.

• Thoughts about Diabetes [Personal Models of Diabetes [18,19]: This assesses beliefs about the seriousness of diabetes and treatment effectiveness. It is validated for use with adults with diabetes [20].

• Self-Care Behaviours: The revised Self-Care Inventory, a measure of perceived adherence to diabetes self-care recommendations [21].

• Fear of Hypoglycaemia Questionnaire (Worry subscale; [22]). This scale and the one below assesses the influence of these concerns on 
self-management and quality of life. Both scales have established validity and reliability in this patient population.

• Fear of Complications Questionnaire [23].

• Social Support Questionnaire [24,25]: The SSQ6 is an abbreviated version of the original 27-item questionnaire. It provides a measure of the number of supportive relationships available and an indication of the level of satisfaction with that support. It has high internal consistency and 
re-test reliability [26].

• A single-item measure of life satisfaction from the Personal Well-Being Index [27].

• Diabetes Knowledge Questionnaire – Revised Michigan Diabetes Knowledge Questionnaire [28].

• Evaluation of the DAFNE course is assessed at 6 weeks using one, 9-item sub-scale of the Health Education Impact Questionnaire [29].

• Adherence to DAFNE principles: This is assessed at the 6 week, 6 and 12 month follow ups using a DAFNE specific Self-Management questionnaire, developed for the present NIHR Psychosocial study, (MREC 08/H0808/53).

### Analysis

The primary analysis will be a linear model of HbA_1c_ at 12 months with baseline HbA_1c_ as a covariate, (which will improve the power relative to the predicted power), using generalised estimating equations (GEE) to control for clustering within courses. The intracluster correlation coefficient coefficient (ICC) will be estimated using the method of moments. Poisson regression (or a zero-inflated Poisson regression if necessary) will be used on the number of hypoglycaemic episodes over 12 months, which should also have more power than a dichotomy of having/not experiencing an episode, again using GEE to account for clustering. We will use an intention to treat analysis, but will explore the issue of participants dropping out using multiple imputations. The full analysis set (FAS) for the intention to treat analysis includes all patients for whom baseline data was collected. A per protocol analysis will also be performed.

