# The 5x1 DAFNE study protocol: a cluster randomised trial comparing a standard 5 day DAFNE course delivered over 1 week against DAFNE training delivered over 1 day a week for 5 consecutive weeks

**DOI:** 10.1186/1472-6823-12-28

**Published:** 2012-11-08

**Keywords:** Type 1 diabetes, Education, Teaching, Training programs

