### Sample size

Using a non-inferiority design, and based on clinically relevant difference of HbA_1c_ of 0.5%, a standard deviation of 1.5 and groups of 7–8 participants per randomisation group, for 80% power at one-sided 5% significance 150 participants were required to complete the study procedures. Allowing for a 10% drop-out from randomisation to completion of the trial, it was anticipated that we would require 166 subjects to be randomised in the study. Thus we aimed to run 24 courses (12 courses per arm). Each centre was required to recruit 32 patients to enable 4 courses (two standard DAFNE and two 5 week) to be run with 8 participants on each. However, during the recruitment phase of the trial it became apparent that the drop-out rate between randomisation and course participation was higher than had been anticipated, at over 11%, hence one centre ran an extra pair of courses.

The flow of patients through the trial is shown in Figure 1, this figure follows the CONSORT approach, as will future reporting of the trial results [9].

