### Randomisation

After consent and completion of baseline data collection, the participants were individually randomised using a random block size, stratified by centre and a web-based remote randomisation system into either a 1 week course or a 5 week course. The allocation sequence was generated by [name] using a computer program called RANDOLOG (University of Southampton). The centres sent a list of participant study numbers to CE, the project manager, who performed the blinded randomisation and informed the centres of the results.

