### The intervention

Patients were randomised to either:

• 1 week - The standard DAFNE 1 week course, or

• 5 weeks - The DAFNE course delivered on one day a week over 5 consecutive weeks

Although pragmatic in design, in order to try to reduce bias, each Centre’s 1 week and 5 week courses were delivered by the same two DAFNE educators, so that the skills, enthusiasm or teaching style of an educator did not favour one arm over the other. As defined for standard DAFNE courses, a participant was deemed to have completed the course if they attended for at least 4 full days of the 5 day course. Where a participant missed a day, attempts were made by the educators to cover missed material on an individual basis also as per normal DAFNE procedures. If a course could not be filled with trial participants, individuals undergoing DAFNE training but not consented to the trial (‘fillers)’ were included so as to maintain the normal dynamics of DAFNE group education.

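### The stated primary model leaves out centre, the stratification factor; if centre variance remains after baseline adjustment, its standard error is too large and the non-inferiority test loses power

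*Protocol article*

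**What the plan says.** The Randomisation section says participants were "individually randomised using a random block size, stratified by centre". Under The intervention, each centre's 1 week and "5 week courses were delivered by the same two DAFNE educators". The Sample size section has each centre run two courses per arm. Under Outcomes, HbA1c "was measured at local laboratories DCCT aligned"; that one laboratory served both arms of a centre is a fair inference but is not stated.

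The Analysis section specifies a linear model for 12-month HbA1c with baseline HbA1c as covariate, "using generalised estimating equations (GEE) to control for clustering within courses", and a method-of-moments ICC. It names no centre term and no centre level of clustering. It does not say that centre is excluded.

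The title calls the study "a cluster randomised trial comparing a standard 5 day DAFNE course", which does not match the individual randomisation described in the text.

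**The concern.** Each centre contributes courses to both arms, with shared educators, a shared patient pool and probably a shared laboratory. Whatever raises or lowers HbA1c in a whole centre does so in both arms, and drops out of the difference between them. The true sampling variance of the treatment effect therefore contains no centre component.

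A GEE clustered on course, without a centre term, does not use this. It sees course means that differ partly because centres differ, counts that as random variation between independent courses, and carries it into the standard error. In a non-inferiority trial one confidence limit decides the answer, so a standard error that is too large pushes that limit towards the margin for no reason. At stake is power: a 5 week course that is non-inferior might fail to be shown so.

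**Working it through.** **Inputs from the article.** Seven centres; individual randomisation stratified by centre; two courses per arm per centre; a non-inferiority margin of 0.5 HbA1c percentage points; 150 completers for 80% power at a one-sided 5% level; and, for spread and group size, "a standard deviation of 1.5 and groups of 7–8 participants per randomisation group". The number of courses is 24 as planned, or 7 × 4 = 28 from the per-centre requirement, or 30 with the extra pair that one centre ran.

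**Inputs that must be assumed.** The article gives no course ICC, centre variance or standard error, so there is no plan figure on this point to reproduce. Assumed: course ICC 0.02; 6.3 completers per course (close to 150/24 = 6.25); centre share of residual variance 0 to 10%.

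**Step 1: algebra.** Set the total residual variance to 1, with centre share vc, course share vk and individual share ve = 1 − vc − vk, and m completers per course.

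- Variance of a course mean as the course-only model sees it: vc + vk + ve/m.
- Variance that matters for the within-centre comparison: vk + ve/m.
- SE ratio = √[(vc + vk + ve/m)/(vk + ve/m)].

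With vk = 0.02 and m = 6.3:

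- vc = 0: ratio 1.00.
- vc = 0.02: ve/m = 0.96/6.3 = 0.1524; √(0.1924/0.1724) = 1.06.
- vc = 0.05: ve/m = 0.93/6.3 = 0.1476; √(0.2176/0.1676) = 1.14.
- vc = 0.10: ve/m = 0.88/6.3 = 0.1397; √(0.2597/0.1597) = 1.28.

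This is slightly generous. With 14 courses per arm in seven pairs, the sample variance of course means carries 12/13 of vc, not all of it. For vc = 0.10 that gives √[(0.0923 + 0.1597)/0.1597] = 1.26.

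**Step 2: simulation.** Layout: 7 centres × 4 courses × 7 completers (196), SD 1.5, margin 0.5, course ICC 0.02, 4,000 trials per setting. Both analyses use a small-sample-corrected variance and a t reference, so they differ only in the centre term. The nominal one-sided error is 5%.

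| Centre share | SE ratio, course only | Error, course only | Error, centre fitted | Power, course only | Power, centre fitted |
|---|---|---|---|---|---|
| 0 | 1.00 | 5.1% | 5.4% | 70% | 69% |
| 2% | 1.05 | 4.2% | 5.2% | 66% | 69% |
| 5% | 1.15 | 3.1% | 5.2% | 62% | 70% |
| 10% | 1.30 | 1.7% | 4.6% | 55% | 70% |

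Monte Carlo standard errors are about 0.3 percentage points for the error rates (√(0.05 × 0.95/4000)) and 0.7 for power. The power levels use the unadjusted SD of 1.5; baseline adjustment would raise both columns.

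**Step 3: effect on the limit.** The simulated true SE was 0.219 at a 5% share and 0.214 at 10%. With a multiplier of about 1.7, the upper limit moves out by 0.219 × 0.154 × 1.7 ≈ 0.06 and 0.214 × 0.298 × 1.7 ≈ 0.11 HbA1c percentage points, against a margin of 0.5.

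**Step 4: sensitivity.** With 24 courses of 6.25 completers, the corrected SE ratios at centre shares of 0, 2%, 5% and 10% are 1.01, 1.07, 1.16 and 1.30 for a course ICC of 0, and 0.98, 1.02, 1.10 and 1.20 for a course ICC of 0.05. A separate run with residual SD 1.2 and 28 courses gives course-only error of 4.9%, 4.2%, 3.3% and 2.3%. The pattern does not depend on the layout or the SD.

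**The case against.** **No centre variance is documented.** A reader might infer that the standard error is simply wrong. The article does not support that. If nothing is left between centres after baseline adjustment, the inflation is zero. DCCT-aligned assays limit laboratory differences, and baseline HbA1c would absorb part of a stable laboratory offset. This stands, and it is why the size is given as a range that starts at nil.

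**The article is condensed.** Centre is not excluded, and a fuller plan may include it. That is fair. However, the Analysis section goes as far as fixing the estimator, the covariate, the clustering unit and the ICC method, and the only stratification factor named in the article is not in that list.

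**Few clusters.** A reader might also infer that a GEE with so few courses inflates the error rate. An uncorrected sandwich variance with a normal reference would give about 6.1% at zero centre variance. The two effects would then offset: 5.3% at a 2% share and 4.9% at 3%, with little power to gain from fitting centre (84% without against 82% with centre at 2%; 81% against 83% at 5%). But the article states neither an uncorrected variance nor a normal reference, and that choice is normally left to the analysis plan. It is not an error in this document.

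**Alternatives.** A mixed model instead of GEE, or a within-centre ICC, would be a preference among valid options.

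**Conclusion.** The point holds as a conditional one. The stated primary model does not use the stratification by centre. If centre variance remains after baseline adjustment, the course-only standard error is too large: by about 6%, 14% or 28% at centre shares of 2%, 5% or 10%, assuming a course ICC of 0.02 and about 6.3 completers per course, and by nothing at a share of zero. The test is then conservative. In the like-for-like simulation, power is 66%, 62% and 55% instead of about 69–70%. Leaving out centre does not make a false claim of non-inferiority more likely.

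The title contradicts the Randomisation section, and no assumption is needed to see it. A reader might infer from the title that whole courses were allocated; the text says individuals were. This is a labelling matter: clustering by course is already handled in the analysis, so no result changes.

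**What to change.** Add centre as a fixed effect to the primary HbA1c model and keep course as the cluster in the GEE. If a fuller analysis plan already does this, say so where the primary model is stated. With 24 to 30 courses, a small-sample-corrected variance with a t reference is advisable.

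The cost is analysis wording and six degrees of freedom for seven centres: with 28 courses, 28 − 7 − 1 = 20 remain at course level instead of 28 − 2 = 26. If centre variance is nil, power falls slightly (70% to 69% in the like-for-like simulation). Against an uncorrected sandwich with a normal reference the drop would be from 85% to 82% at residual SD 1.2, mostly because that analysis exceeds its nominal error rate.

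Replace the cluster-randomised label in the title with wording that says participants were individually randomised and treated in groups.
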